### Outcome measures

2.10

All baseline assessments will be completed within 7-days prior to commencing the intervention and follow-up will occur as per our assessment schedule (Table 3). Self-reported outcome measures will be recorded *via* RedCap® and will take 20–30 ​min for each participant. Physical assessment measures will be recorded by the principal investigator and research assistant directly into RedCap®. Physical assessments will occur at the Edith Cowan University neurophysiology laboratory, in accordance with existing standard operating procedures, and are expected to take ∼120 ​min.

**Table 3 tbl3:** STIM-Hips study assessment schedule.

	Variable	Weeks			
		0	4	8 (post-intervention)	16
Primary outcome variable	The International Hip Outcome Tool–33	x	x	x	x
Secondary outcome variables	Motor cortex excitability	x		x	
	Voluntary activation	x		x	
	Conditioned pain modulation	x		x	
	EuroQol 5 dimensions	x	x	x	x
Other variables	Demographics	x		x	
	Kellgren Lawrence (KL) Score	x			
	Scoring hip osteoarthritis with MRI (SHOMRI)	x			
	Flare-Osteoarthritis questionnaire	X	X	X	X
	Sit to stand pain	x		x	
	Muscle strength	x		x	
	Medication	x	x	x	x
	Physical activity	x	x	x	x
	Work status	x	x	x	x
	Dietary intake	x			
	Lifestyle Measures	x			
	Psychological Measures	x			
	Adherence	Continual			
	Adverse events	Continual			

#### Primary outcome variable

2.10.1

##### Pain, Disability and QoL

2.10.1.1

The International Hip Outcome Tool–33 (iHOT-33) is a valid and reliable tool to assess pain, disability and quality of life in people with hip OA, and recommended by the 2018 Zurich consensus [17]. The iHOT-33 has a range of scores from 0 to 100 and a minimal important change (MIC) of 12.5 points [18].

#### Secondary outcome variables

2.10.2

##### Motor cortex excitability

2.10.2.1

Transcranial magnetic stimulation (TMS) is a valid method that elicits quadriceps motor responses, assessing cortex excitability/inhibition including: motor evoked potential; resting/active motor threshold; short-interval intracortical inhibition; intracortical facilitation; silent period [16].

##### Voluntary Activation

2.10.2.2

Voluntary activation of the quadriceps will be assessed by generating an electrically evoked muscle twitch, using supramaximal femoral nerve stimulation, which will be superimposed onto a maximal voluntary knee extension force (MVC) and then performed with the muscles at rest. Voluntary activation (%) will be calculated as (1 ​− ​superimposed twitch amplitude/resting twitch amplitude) × 100. Participants will be in a seated position and performing a maximal knee extension in our custom-built chair. The participant will be familiar with the MVC procedure from their peripheral muscle strength testing with trials structured in an identical manner. Stimulation intensity will be identified by gradually increasing intensity until the resting knee extensor twitch response is maximal [19].

##### Conditioned pain modulation

2.10.2.3

Pressure pain thresholds (kiloPascals, kPa) of the hip, over the superior border of the greater trochanter, and the ipsilateral lateral epicondyle of the elbow, assessed using an algometer, will be used as the test stimulus and icy cold water (∼5 ​°C) immersion of the hand (contralateral hand to the most painful hip) for 3 ​min as conditioning stimulus [20]. The CPM effect will be calculated as the absolute (kPa) and relative (percentage) pre-post ice immersion pressure pain threshold change [10,21].

##### Health-related QoL

2.10.2.4

The EuroQol 5 dimensions (EQ-5D-5L) is a valid and reliable tool to quantify health-related QoL [22].

#### Other variables

2.10.3

##### Demographic data

2.10.3.1

Age (years), sex (male; female; intersex), race (White; Black or African American; American Indian or Alaska Native; Asian; Native Hawaiian or Other Pacific Islander), height (cm), weight (kg), duration of hip pain (weeks), education level (Less than high school; High school graduate; Bachelor's degree; Master's degree; Doctoral degree; Professional degree), occupation, employment status (Full time; Part time; Home maker; Student; Retired; Other) and household income (Less than 30,000 AUD; 30,000–49,999 AUD; 50,000–79,999 AUD; 80,000–99,999 AUD; 100,000–149,999 AUD; 150,000–199,999 AUD; Greater than 200,000 AUD; Decline to answer).

##### Severity of radiographic OA

2.10.3.2

Assessed *via* x-ray using the Kellgren Lawrence (KL) scoring system and *via* MRI using the Scoring Hip Osteoarthritis with MRI (SHOMRI), reported by a single radiologist from the partner radiology clinic. The KL score will be an ordinal score between 0 and 4, with scores of 2 or greater representing radiographic osteoarthritis [23]. The SHOMRI score will include the assessment of eight core hip joint features (articular cartilage lesions, bone marrow oedema, subchondral cysts, labral abnormalities, paralabral cysts, intra-articular loose bodies, joint effusion, and ligamentum teres abnormalities) with an ordinal score assigned to each feature [24].

##### Flare-OA Questionnaire

2.10.3.3

The Flare-OA Questionnaire is a valid and reliable tool to evaluate the presence and severity of any OA flare [25].

##### Pain with sit-to-stand

2.10.3.4

The 11-point numerical rating scale of pain (NRS-P) will be used to determine pain from a functional activity that is provocative in hip OA. The squat depth will be standardised to a set height (standard 20-inch gym box) and patients will be provided standardised instructions to report the worst NRS-P from five repetitions.

##### Hip and knee muscle strength

2.10.3.5

Maximal isometric hip abduction, hip adduction, hip flexion, hip extension and knee flexion strength [26] will be measured using a hand-held dynamometer. Participants will perform several submaximal tests to familiarise themselves with each action before completing three maximal voluntary contraction (MVC) tests, pushing for 3 ​s per trial and with a minimum of 30-s rest between trials. We will record peak force within each trial to calculate the average force, the maximal force and the co-efficient of variation of the three trials. The distance from the greater trochanter to the dynamometer (hip measures) and patellar apex to dynamometer (knee measures) will be measured to allow calculation of torque. An identical approach will be used for knee extension, however this will be performed in a custom-built chair with the ankle secured within a splint connected to a force transducer, prior to TMS, as quadriceps maximal contraction strength will determine TMS/voluntary activation parameters. Participants will be positioned to ensure consistent, controlled contractions during assessment.

##### Medications

2.10.3.6

All medications (pain and general medications) will be recorded.

##### Physical activity level

2.10.3.7

The World Health Organisation Global Physical Activity Questionnaire (GPAQ) [27] will be used to quantify physical activity levels.

##### Lifestyle measures

2.10.3.8

Smoking status (Yes/No) and alcohol intake (drinks per week) will also be recorded prior to physical assessment.

##### Psychological measures

2.10.3.9

The generalised anxiety disorder (GAD-7) [28], patient health questionnaire (PHQ-9) [29] and depression, anxiety and stress scale (DASS) [30] will be completed. The 11-item TAMPA Scale of Kinesiophobia will be used to assess the extent of fear of movement in participants [31].

##### Exercise and consultation adherence

2.10.3.10

Exercise adherence will be recorded as the number of consultations attended, which will be extracted from the clinical records at the conclusion of the intervention window.

##### Adverse events

2.10.3.11

Adverse events will be directly reported to study staff and recorded with date, time and description of incident/event.

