### Intervention

2.9

[name] will train partner physiotherapists in delivering the tDCS and exercise-based interventions for STIM-Hips. The exercise rehabilitation intervention will be identical between groups and will be reported as per the Consensus on Exercise Reporting Template (CERT) [15] in Table 2. Participants will be provided an 8-week gym membership at the provider physiotherapy clinic. The intervention will involve 8 weeks of physiotherapist-supervised exercise, consisting of three in-person visits/week in which participants receive tDCS during each session. Exercise will be based on templates, sent *via* Physitrack®, however these will be individually adapted as able and progressed when participants can complete the prescribed exercise.

**Table 2 tbl2:** Consensus on exercise reporting template.

Item	Protocol
Detailed description of the type of exercise equipment	The majority of exercises will use body weight resistance, however the following additional equipment will be utilised: knee extension machine, hamstring curl machine, leg press machine, circular TheraBand.
Detailed description of the qualifications, expertise and/or training	All exercises will be prescribed by a qualified physiotherapist, with greater than two years of experience in managing chronic hip pain.
Describe whether exercises are performed individually or in a group	Exercises will be prescribed individually and performed individually, however there may be other rehabilitation patients and clinicians in the rehabilitation gymnasium at the same time.
Describe whether exercises are supervised or unsupervised; how they are delivered	Participants will receive 1:1 supervision by a physiotherapist for one rehabilitation session per fortnight (which will include progressing exercises). All other rehabilitation sessions will be unsupervised.
Detailed description of how adherence to exercise is measured and reported	Attendance at the rehabilitation centre will be recorded *via* private practice standard booking system.
Detailed description of motivation strategies	Participants will receive reminder text messages about physiotherapy consultations.
Detailed description of the decision rule(s) for determining exercise progression	All exercises will be prescribed so they are either pain free or have minimal pain (≤2/10 on a numerical rating scale of pain) when performed. Exercises will be progressed when all sets and repetitions can be performed.

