Detailed description of how the exercise program was progressed	Not applicable.
Detailed description of each exercise to enable replication	The exercise progressions will be based on patient function but must include: • A single joint exercise for each of the following muscle groups: lumbar extensors; abdominals; hip extensors; hip flexors, hip abductors; hip adductor; knee flexors; knee extensors; ankle plantar flexors. • A multi joint squat pattern (e.g., squat) and bend pattern (e.g., deadlift) movement. • One balance-based exercise (e.g., star excursion balance).
Detailed description of any home programme component	Not applicable.
Describe whether there are any non-exercise components	The additional intervention is provided below.
Describe the type and number of adverse events that occur during exercise	Adverse events will be reported to all study staff as they occur.
Describe the setting in which the exercises are performed	Exercises will be performed in a physiotherapy rehabilitation gymnasium.
Detailed description of the exercise intervention	Participants will be provided double leg single joint exercises (e.g., double leg bridge), before being progressed to single leg single joint exercises (e.g., single leg bridge) and then more highly loaded single leg single joint exercises (e.g., single leg hip thrust). Sets and repetitions will be based on endurance repetitions (e.g., 3 ​× ​15 reps) and performed three times per week.
Describe whether the exercises are generic (one size fits all) or tailored	Exercises will follow the description above but will be individually tailored to the participant and progressed as able.
Detailed description of how exercises are tailored to the individual	Exercises will be progressed when participants can perform 3 ​× ​15 repetitions or regressed if they are causing pain >2/10.
Describe the decision rule for determining the starting level	All participants will be commenced with double leg single joint exercises and progressed as able.
Describe how adherence or fidelity is assessed/measured	Adherence will be determined as the number of sessions attended across the 8-week intervention divided by the number of prescribed sessions.
Describe the extent to which the intervention was delivered as planned	Not applicable.

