The tDCS devices (Brain Premier tDCS E1 Plus) will deliver a weak current [2 milliamps (mA)] from a 35 ​× ​35 ​mm anodal electrode [that increases cortical excitability [16]] on the scalp at the vertex (overlying primary motor cortex of the more symptomatic limb) to a cathodal electrode placed over the deltoid tubercle on the upper arm. The physiotherapist will also train the participant in how to self-perform tDCS on non-supervised days, and will be available to provide assistance if needed during non-supervised sessions. Other than electrical stimulation, real and sham procedures are identical. Real tDCS will be performed at 2 ​mA for 20 ​min whilst completing exercise rehabilitation. Sham tDCS will be applied during exercise with the placebo setting active, ramping to give the sensation of tDCS, then dropping to no output with the screen falsely reporting 2 ​mA of output.

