### Adverse events

2.11

tDCS has an excellent safety profile [32]. tDCS has few adverse events when applied with stimulation parameters in line with published guidelines. Adverse events from tDCS are rare or mild, with mild tingling/itching of the scalp most common [6,7,32].

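### Adverse events are captured only as they are reported, while under Table 2 20 of 24 tDCS sessions are unsupervised and self-applied, so mild scalp effects may be under-recorded

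*Protocol article*

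**What the plan says.** The article describes adverse-event capture in three places, and each description is driven by the event:

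- Section 2.10.3.11: "Adverse events will be directly reported to study staff and recorded with date, time and description of incident/event".
- Table 2, exercise reporting template: "Adverse events will be reported to all study staff as they occur".
- Table 3, assessment schedule: "Adverse events Continual". The entry is not tied to weeks 0, 4, 8 or 16.

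Section 2.11 states what is expected: "Adverse events from tDCS are rare or mild, with mild tingling/itching of the scalp most common".

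On supervision, section 2.9 gives two accounts. The prose reads: "The intervention will involve 8 weeks of physiotherapist-supervised exercise, consisting of three in-person visits/week in which participants receive tDCS during each session". Table 2 reads: "Participants will receive 1:1 supervision by a physiotherapist for one rehabilitation session per fortnight", and then "All other rehabilitation sessions will be unsupervised". The later paragraph of section 2.9 on the devices agrees with the table that some days are not supervised: "The physiotherapist will also train the participant in how to self-perform tDCS on non-supervised days". It adds that the physiotherapist can be asked for help at those sessions. Table 2 places all exercise in a physiotherapy gymnasium, and section 2.12 gives each participant a chat group that includes the trial coordinator and the supervising physiotherapist.

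**The concern.** The method as described records an event when somebody reports it. The effects the article expects are mild and brief, and participants may take them to be a normal part of stimulation, particularly as the sham is designed to produce the same sensation. Such effects are easily left unmentioned when nobody asks. On the Table 2 schedule, most stimulation takes place with no supervising physiotherapist assigned to the session.

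Participants already answer self-report questionnaires at weeks 0, 4, 8 and 16, but none of the instruments listed in Table 3 covers stimulation effects. The recorded fields are date, time and description, so severity is not captured in a standard form either.

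What is at stake is the interpretation of the safety data. A low count could be taken as support for the favourable safety profile described in section 2.11 when part of it reflects the absence of a question. The primary iHOT-33 analysis is not affected.

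**Working it through.** The article gives no adverse-event figure to reproduce. What can be checked is the share of sessions without supervision, and what incomplete capture would do to a by-arm summary.

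**Sessions per participant (section 2.9 and Table 2)**

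- Total: 8 weeks × 3 per week = 24, with tDCS at each.
- Supervised under Table 2: one per fortnight, 8 / 2 = 4.
- Unsupervised: 24 − 4 = 20, and 20 / 24 = 83.3%.
- Per arm, with 39 participants: 39 × 24 = 936 planned sessions, of which 39 × 20 = 780 are unsupervised.
- Whole trial, with 78 participants: 1,872 planned sessions, of which 1,560 are unsupervised.

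These are planned counts before dropout. If the section 2.9 prose were read as supervision at every session, the unsupervised count would be 0 of 24. The two statements cannot both describe the same schedule. The training in self-applied tDCS presupposes non-supervised days, as Table 2 does.

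**Is there any scheduled enquiry?**

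- Table 3 schedules the iHOT-33, EQ-5D-5L, Flare-OA questionnaire, medication, physical activity and work status at weeks 0, 4, 8 and 16. None is an enquiry about scalp, skin or headache symptoms after stimulation.
- Help from the physiotherapist is given if needed, and the chat group is for open communication. Neither is described as a routine question.

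**Effect of incomplete capture (illustration)**

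The rates here are assumptions, not figures from the article. Suppose 60% of the real arm and 30% of the sham arm have a scalp symptom, and a fraction c of these is recorded. The recorded difference is c × (0.60 − 0.30). With equal capture, the ratio is (0.60c) / (0.30c) = 2.0 whatever c is.

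| Capture, both arms | Recorded difference | Risk ratio |
|---|---|---|
| 100% | 30 points | 2.0 |
| 75% | 22.5 points | 2.0 |
| 50% | 15 points | 2.0 |
| 25% | 7.5 points | 2.0 |

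The ratio moves only if capture differs by arm:

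- 60% real and 40% sham: (0.60 × 0.60) / (0.30 × 0.40) = 0.36 / 0.12 = 3.0.
- 40% real and 60% sham: (0.60 × 0.40) / (0.30 × 0.60) = 0.24 / 0.18 = 1.33.

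Equal under-capture therefore lowers the counts and the absolute difference. Distortion of the ratio needs a further condition that the article does not establish.

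**The case against.** The strongest reply is that this is a condensed article. The wording of adverse-event questions and the case report form commonly sit in the full protocol, and section 2.10.3.11 says neither who reports nor whether staff ask. Reading it as purely spontaneous reporting is an inference. That stands as a limit on certainty. It does not remove the point, because the article does state a method, three times, and each statement has events arriving as they happen.

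The setting also mitigates. Sessions are on clinic premises, a physiotherapist can be called on, supervised contact comes every fortnight, and a direct messaging channel exists. These make a troublesome event less likely to be missed. As described, though, the help and the channel depend on the participant raising the matter, which is the weak link for mild effects.

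A reader might go further and infer that scalp effects will be undercounted, or that a real-versus-sham safety comparison is biased. The document supports neither. It gives no event rate or capture rate, so an undercount is possible but not shown. It plans no formal safety comparison: safety is not among the objectives in section 1.2, adverse events are listed under other variables, and section 3.1 names between-group analyses only for the iHOT-33, cortex excitability and conditioned pain modulation. What remains is the general statement in section 3.1 that all data will be described. Capture could differ by arm, since real stimulation runs for 20 minutes at 2 mA while sham drops to no output after the ramp, but that is conjecture.

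**Conclusion.** The point holds as a limitation of the stated method. Capture is described only as reporting when events occur, and on the Table 2 schedule 20 of 24 tDCS sessions (83%) are unsupervised and self-applied. Mild scalp effects may be under-recorded, and any descriptive summary of adverse events by arm should be read with that limit.

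The 83% rests on Table 2 being the operative schedule, which the conflicting prose of section 2.9 leaves open. The conclusion also assumes that no symptom enquiry exists in a fuller document; if one does, the point reduces to stating it in the article. The size of any undercount cannot be derived from the article. This is a worthwhile and inexpensive improvement to the safety data and has no bearing on the sample size or the primary analysis.

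**What to change.** 1. Reconcile the section 2.9 prose on supervision with Table 2, so that it is clear how many of the 24 sessions a physiotherapist supervises.
2. Keep reporting as events occur. Add a short solicited checklist, with severity for each item, to the existing REDCap questionnaires at weeks 4 and 8: tingling, itching, burning, headache, skin redness or lesion, other. Use the same wording in both arms. Week 16 is not needed, because it falls eight weeks after stimulation ends.
3. Place the checklist after the iHOT-33 and do not ask whether the symptom was related to stimulation. Both choices limit the chance of prompting a guess about allocation before or while the participant rates the primary outcome.
4. Send the answers to a staff member who does no outcome assessment.
5. Report solicited and spontaneously reported events separately by arm.

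The cost is one additional page at two existing time points, with no new visits. There are three drawbacks. Counts will be higher in both arms. Recall of transient effects is imperfect, since each form looks back over 4 × 3 = 12 sessions. A small risk of prompting allocation guesses remains.

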### Adverse events

2.11

tDCS has an excellent safety profile [32]. tDCS has few adverse events when applied with stimulation parameters in line with published guidelines. Adverse events from tDCS are rare or mild, with mild tingling/itching of the scalp most common [6,7,32].

### Team and participant communication

2.12

Once enrolled, all participants will be added to their own individual WhatsApp chat group with the clinical trial coordinator, supervising physiotherapist, and [name] to allow for open dialogue.

### Power calculation

2.13

Using G∗Power v3: *n* ​= ​64 is sufficient to detect between-group differences if greater than the iHOT-33 MIC ​= ​12.5 points (*d* ​= ​0.71) [19], *α* ​= ​0.05, 1-*β* ​= ​0.80. Thus, we will recruit *n* ​= ​78 hip OA participants (*n* ​= ​39 per arm) accounting for an expected portion being lost to follow-up (drop-out ∼20% expected from pilot studies in knee OA [6]).

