### Participants

2.6

Recruitment of 78 consenting, adult participants (39 per arm) with a clinical and radiological diagnosis of hip OA will be undertaken (includes accounting for dropouts). The clinical and radiological diagnosis will be made *via* a Sports and Exercise Physician. The clinical diagnostic criteria include: activity-related hip pain (>3/10) and a positive Flexion Adduction and Internal Rotation (FADDIR) test. Radiological OA will be categorised as a Kellgren Lawrence score of greater than or equal to 2 [14].

Participants will be excluded for: rehabilitation in past 6-months; previous lower-limb surgery; hip joint injection within 3 months; neurological conditions; cardiometabolic conditions that preclude exercise; inability to commit to rehabilitation; specific transcranial magnetic stimulation, tDCS or CPM contraindications (Table 1); inability to understand English; <40 years of age.

**Table 1 tbl1:** Contraindications to transcranial magnetic stimulation, transcranial direct current stimulation and conditioned pain modulation.

Assessment	Exclusion Criteria
Transcranial magnetic stimulation and transcranial direct current stimulation	Pregnancy
	Neurological conditions/illness, including epilepsy/convulsion/seizure
	Vascular, traumatic, tumorous, infectious, or metabolic lesion of the brain, even without history of seizure, and without anticonvulsant medication
	Previous or current implants in their body that may be triggered or heated by an electrical current (e.g. pacemaker, intracranial shunts, artificial cochlea, etc)
	Any mental implanted in their head (e.g. surgical clips, staples, shrapnel)
	Frequent or intense headaches
	Previous brain trauma or neurosurgical intervention
	Serious medical complications (e.g. advanced pulmonary, cardiac, liver or kidney disease)
Conditioned Pain Modulation	Cold urticaria
	Raynaud's phenomenon

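### Minor arithmetic slip in section 2.13: 78 recruits leave about 62 evaluable at 20% dropout, not the required 64

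*Protocol article*

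**What the plan says.** The Power calculation (section 2.13 of the protocol article) reports from G*Power that "64 is sufficient to detect between-group differences if greater than the iHOT-33 MIC", which is 12.5 points or d = 0.71, at alpha 0.05 and power 0.80. It then moves to 78 participants, 39 per arm, "accounting for an expected portion being lost to follow-up", and gives the loss rate as "drop-out ∼20% expected from pilot studies in knee OA [6". The Participants section (2.6) repeats the target as "Recruitment of 78 consenting, adult participants (39 per arm" and notes in parentheses that dropouts are included.

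Three things are not stated: the formula that takes 64 to 78, whether the test is one-sided or two-sided, and the standard deviation behind d.

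**The concern.** The recruitment target is justified in one way only: it is the required evaluable number, enlarged for expected loss. A reader should be able to apply the stated loss to 78 and arrive at 64 or more. At 20% loss the result falls just below 64.

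To allow for a loss fraction *w*, the required number is divided by (1 − *w*). Multiplying by (1 + *w*) gives too few, because the loss applies to the larger, recruited number. The printed 39 per arm looks like the second calculation. What is at stake is whether the stated sample size follows from its own inputs, and whether the 80% power attached to it still holds at the dropout the trial expects.

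**Working it through.** **Inputs** (section 2.13 unless noted)

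- Required evaluable: 64, that is 32 per arm with 1:1 allocation (section 2.8).
- Standardised difference: d = 0.71, printed to two decimals.
- Alpha 0.05, power 0.80. Two-sided testing is an assumption. One-sided testing would need only 50 to 52 in total, so it does not fit 64.
- Dropout: about 20%.
- Recruited: 78, that is 39 per arm.

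**Step 1. Reproduce 64.** The normal approximation gives n per arm = 2(1.96 + 0.8416)²/0.71² = 31.1, rounded up to 32, so 64 in total. This matches the plan. The exact t-test (noncentral t) at d = 0.71 gives 79.8% at 32 per arm and 81.1% at 33 per arm. That does not count against 64: an unrounded d of 0.7125 gives 80.1% at 32 per arm and 0.7149 gives 80.4%, and both print as 0.71. The 64 is therefore accepted.

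**Step 2. Apply the dropout.**

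| Quantity | Calculation | Result |
|---|---|---|
| Evaluable from 78 at 20% loss | 78 × 0.8 | 62.4 |
| Recruits needed to keep 64 | 64/0.8 | 80 (40 per arm) |
| Largest loss that leaves 64 of 78 | (78 − 64)/78 = 14/78 | 17.9% |
| Multiplying instead, per arm | 32 × 1.2 = 38.4, rounded up | 39 (78 in total) |

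The gap is 80 − 78 = 2 recruits, or 64 − 62.4 = 1.6 evaluable participants. The last row matches the printed figure.

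**Step 3. Convert to power at d = 0.71, two-sided alpha 0.05.**

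| Evaluable per arm | t-test | Normal approximation |
|---|---|---|
| 31 | 78.5% | 79.8% |
| 31.2 (62.4 in total) | 78.8% | 80.1% |
| 32 | 79.8% | 81.1% |

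On the t-test scale, going from 32 to 31 per arm costs 79.8 − 78.5 = 1.3 points. Against the nominal 80% the difference is 80 − 78.5 = 1.5 points, of which 0.2 comes from the rounding in Step 1 and not from dropout.

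**The case against.** The strongest reply has three parts.

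*The dropout figure is approximate.* It carries a tilde, and 17.9% can fairly be called about 20%. On that reading 78 is adequate. This stands as a reason to call the point minor. It does not remove it: 20% is the only planning value given, and an approximate figure can also turn out higher, where the gap widens (at 22% loss 60.8 remain and t-test power is 77.7%).

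*The gap is within ordinary rounding.* Two recruits in 80 and about 1.3 points of power would change no design decision. By the normal approximation, power at 62.4 evaluable is still 80.1%. This also stands, and it limits the weight of the point.

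*The calculation is not the planned analysis.* Section 3.1 plans repeated mixed effects models with covariates, and Table 3 measures the iHOT-33 at weeks 0, 4, 8 and 16. Someone lost after week 4 can still contribute data. If the analysis also adjusts for the baseline score (an assumption; section 3.1 does not list it among the confounders), a baseline–outcome correlation of 0.2 brings 31 per arm to about 80% power, and 0.3 to about 82%. This stands as well, although section 2.13 claims no such gain and justifies 78 through dropout alone.

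A reader might infer more: that the trial is underpowered, or that a multiplication error has been proved. The documents support neither. The loss of power is shown only for a simple two-group t-test at a loss of 20%. The multiplication by 1.2 fits the figures, but no formula is stated and planning for about 18% loss would fit too. A reader might also divide 12.5 by 0.71, obtain an SD of 17.6 and test larger values. That SD is back-calculated from a rounded d and is not a stated input, and how power responds to the SD is a separate matter from the dropout arithmetic.

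**Conclusion.** The point holds as a minor arithmetic error. Taking the stated loss as 20%, 78 recruits leave about 62 evaluable participants, not 64; dividing by 0.8 gives 80. The shortfall is 2 recruits and about 1.3 points of t-test power (78.5% against 79.8%), or 1.5 points against the nominal 80%.

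This rests on two-sided testing, equal arms, d = 0.71 as printed, a two-group comparison of completers, and a dropout of 20% and not somewhat less. If loss stays at or below 17.9%, there is no shortfall. It is not shown that the planned mixed model would miss 80% power.

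**What to change.** Keep 78 and reword section 2.13 so that the target follows from its inputs, for example:

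> With 78 randomised, 64 remain evaluable if loss is at most about 18%; at 20% loss, about 62 evaluable give about 78.5% power at d = 0.71 (two-sided alpha 0.05).

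The parenthesis on dropouts in section 2.6 can then stay as it is. The cost is one sentence and a stated power about 1.5 points less favourable; recruitment and design do not change.

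Two alternatives would also close the gap: randomise 80 (40 per arm), which costs two more participants, or state the power of the planned adjusted model with its assumed baseline–outcome correlation written out.
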